# Multi-Center Randomized Phase II Clinical Trial on Remote Ischemic Conditioning in Acute Ischemic Stroke Within 9 Hours of Onset in Patients Ineligible to Recanalization Therapies (TRICS-9): Study Design and Protocol

**DOI:** 10.3389/fneur.2021.724050

**Published:** 2021-11-03

**Keywords:** acute stroke, ischemic stroke, remote ischemic conditioning, RIC, phase II, clinical trial, TRICS-9

## Abstract

**Aim:** To assess the efficacy of remote ischemic conditioning (RIC) in patients with ischemic stroke within 9 h of onset, that are not candidates for recanalization therapies.

**Sample Size Estimates:** A sample size of 80 patients (40 in each arm) should yield 80% power to detect a 20% difference in early neurological improvement at 72 h at *p* = 0.05, two sided.

**Methods and Design:** TRICS-9 is a phase II, multicenter, controlled, block randomized, open-label, interventional clinical trial. Patients recruited in Italian academic hospitals will be randomized 1:1 to either RIC plus standard medical therapy or standard medical therapy alone. After randomization, RIC will be applied manually by four alternating cycles of inflation/deflation 5 min each, using a blood pressure cuff around the non-paretic arm.

**Study Outcomes:** The primary efficacy outcome is early neurological improvement, defined as the percent change in the National Institute of Health Stroke Scale (NIHSS) at 72 h in each arm. Secondary outcomes include early neurologic improvement at 24 and 48 h, disability at 3 months, rate of symptomatic intracerebral hemorrhage, feasibility (proportion of patients completing RIC), tolerability after RIC and at 72 h, blood levels of HIF-1α, and HSP27 at 24 h and 72 h.

**Discussion/Conclusion:** RIC in combination with recanalization therapies appears to add no clinical benefit to patients, but whether it is beneficial to those that are not candidates for recanalization therapies is still to be demonstrated. TRICS-9 has been developed to elucidate this issue.

**Clinical Trial Registration:**
ClinicalTrials.gov, identifier: NCT04400981.

## Introduction and Rationale

Remote ischemic conditioning (RIC) relies on a transient ischemia being applied to a certain body site with the aim of increasing ischemic tolerance in distant organs by endogenous protective mechanisms (1–3). Although these mechanisms remain elusive, evidence supports the role of both humoral and neuronal factors, such as the release of adenosine, bradykinin, and nitric oxide in the blood, and the activation of neuronal p-AKT and several miRNAs (4). Recent observations have suggested that HSP27 and HIF-1α are mediators of remote ischemic conditioning and hence potential biomarkers (5–12). Many experimental studies on animal models of ischemic stroke have demonstrated that RIC is neuroprotective against cerebral ischemia and that benefit is obtained in stroke models with or without reperfusion up to 6 h after stroke induction (13–19). Despite numerous preclinical studies, clinical evidence is limited. Clinical studies showed that remote ischemic conditioning, applied by transient limb ischemia using a blood pressure cuff, is well-tolerated, feasible, and safe (20, 21) and that long-term treatment decreases the recurrence risk of stroke due to symptomatic intracranial arterial stenosis (22). Two clinical trials on RIC in combination with intravenous thrombolysis or mechanical thrombectomy gave neutral results (23, 24); however, no studies have investigated whether RIC is beneficial to patients with acute ischemic stroke who are not candidates for recanalization therapies. These patients represent a significant proportion of those with acute ischemic stroke and although criteria for patient eligibility are continuously evolving, the proportion of ischemic strokes potentially eligible for endovascular thrombectomy or intravenous thrombolysis is limited (25, 26).

The Italian Stroke Organization (ISO) Basic Science Network, a nationwide network that promotes translational research on acute ischemic stroke, has launched a multicenter translational research program on RIC. This program provides for a multi-center pre-clinical study of experimental ischemic stroke (27) and a multi-center randomized phase II clinical trial on remote ischemic conditioning in patients with acute stroke within 9 h of onset who are not candidates for recanalization therapies (TRICS-9).

The TRICS-9 trial is designed to investigate the efficacy of RIC in a carefully selected population of ischemic stroke patients whose neurological improvement could be attributed to no acute treatments but RIC, to evaluate the potential role of RIC as acute therapy for patients that are not a candidate for recanalization therapies and who would otherwise receive secondary prevention only.

The study protocol of the clinical trial is described hereafter.

## Methods and Analysis

### Design

The study is a phase II, multicenter, controlled, block randomized, open-label, interventional clinical trial comparing RIC plus standard medical therapy to standard medical therapy alone, in patients with acute ischemic stroke within 9 h of onset that are not eligible to intravenous thrombolysis and/or mechanical thrombectomy. The study has a prospective randomized open blinded end-point (PROBE) (28) design.

### Selection/Treatment of Subjects

Patient enrollments (Figure 1) will be carried out in three ISO-associated academic hospitals provided with Comprehensive Stroke Centers of the Italian Hub-and-Spoke network for stroke. Patients will be eligible for inclusion in the trial if they have evidence of acute ischemic stroke due to either small or large vessel occlusions of the anterior circulation within 9 h of symptom onset, are 18 years of age or older, have a score on National Institutes of Health Stroke Scale (NIHSS; scores range from 0 to 42, with higher scores indicating a more severe deficit) equal to or higher than 5 and lower than 25, a pre-stroke score of 0 or 1 on the modified Rankin scale (which ranges from 0 to 6, with a score of 0 indicating no disability and higher scores indicating more severe disability), and patients or they surrogate provided informed consent. Strokes with unknown time of onset will also be considered for enrollment. For patients with stroke symptoms on awakening, the midpoint of sleep (i.e., the time between going to sleep and waking up with symptoms) will be considered as time of stroke onset and patients will undergo randomization if the estimated time of onset is ≤ 9 h (29); for patients with neurologic deficits (e.g., aphasia, anarthria, altered mental status) that keep them from reporting the time of onset, enrollment will be possible whenever the time elapsed since the patient was last known to be well is ≤ 9 h. Information regarding the time of going to sleep or the last time the patient was seen well will be obtained by the patient or anyone who last had contact with the patient before stroke onset. Patients eligible for either or both intravenous thrombolysis and mechanical thrombectomy will be excluded from the trial. Other exclusion criteria will be evidence of intracranial hemorrhage, vascular malformation, intracranial masses on brain CT or MRI, rapidly improving neurological symptoms at the time of first evaluation, transient ischemic attack with the resolution of symptoms at the time of first evaluation, amputation of the upper non-paretic arm, ulcers, phlebitis, or bad skin condition in the upper limbs, and history of peripheral artery disease or sickle cell disease. All inclusion and exclusion criteria are summarized in Table 1.

**Figure 1 F1:**
[figure not shown]
Flowchart of TRICS-9.

**Table 1 T1:** Inclusion and exclusion criteria.

**Inclusion criteria**
• Clinical diagnosis and/or diagnosis on neuroimaging of anterior circulation acute ischemic stroke (due to either large or small vessel occlusion) within 9 h of symptom onset • Age ≥ 18 years • NIHSS ≥5 and <25 • Stroke with Unknown Time of Onset: this will include wake up strokes with estimated time of onset ≤ 9 h of enrollment or patients unable to report symptom onset but that were last known to be well ≤ 9 h of enrollment • Modified Rankin scale ≤ 2 prior to stroke onset • Written informed consent obtained from patient or legally responsible person
**Exclusion criteria**
• Candidates for intravenous thrombolysis and/or mechanical thrombectomy according to AHA/ASA guidelines • Brain CT or MRI detecting intracranial hemorrhage, vascular malformation, intracranial masses, or any medical condition unrelated to stroke that could explain symptoms • Rapidly improving neurological symptoms at the time of first evaluation • Transient ischemic attack • Amputation of the upper non-paretic arm • Ulcers or a bad skin condition in the upper limbs • History of peripheral artery disease, sickle cell disease, or upper limb phlebitis • Pregnancy • Ongoing participation in any interventional study • Terminal illness or life expectancy ≤ 6 months • Patients unable to give informed consent

*CT, computed tomography; MRI, magnetic resonance imaging; NIHSS, National Institutes of Health Stroke Scale*.

### Randomization

Participants will be randomly assigned to either control or experimental groups with a 1:1 allocation as per computer-generated block randomization schedule stratified by site. A specific “Randomization Procedure” document will be prepared, signed, and stored within a sealed envelope before the first randomization, The allocation sequence will be created by an individual separated from trial investigators and analysts. Treatment allocation will be disclosed after the patient has been recruited.

### Interventional Method

The experimental intervention will be performed in the Emergency Department immediately after randomization. A standard blood pressure cuff will be placed around the non-paretic arm. Patients randomized to RIC will undergo remote ischemic conditioning by four cycles of intermittent, manually induced, upper limb ischemia alternating 5 min of inflation (20 mmHg above the systolic blood pressure) to 5 min of deflation. Patients in the control group will have the blood pressure cuff placed around the non-paretic arm for 40 min but will undergo no inflations. All patients will receive usual care, at the discretion of the investigator and according to available guidelines and standards of care.

### Outcomes

Admission NIHSS will be assessed before randomization, whereas NIHSS at 72 h (NIHSS72) will be obtained by a neurologist blinded to treatment allocation.

The primary efficacy outcome will be early neurological improvement at 72 h, defined as percent change in NIHSS score [(Admission NIHSS—NIHSS72) × 100/Admission NIHSS]. This definition has been adopted in a recent study that re-assessed the primary outcome of the NINDS part 1 trial on intravenous thrombolysis, wherein percent change in NIHSS score resulted to be more sensitive in demonstrating early clinical benefit and more predictive of long-term neurological outcome (30, 31) than the absolute changes in NIHSS score.

### Sample Size Estimates

In the NINDS trial, the NIHSS percent change in the control group was 15% +/– 35% at 24 h. The median of the NIHSS percent change in absence of treatment is expected to slightly increase, and the standard deviation to slightly decrease, at 72 h, due to stabilization of the neurological deficit. An estimated total sample size of 80 patients (40 patients in each arm) should yield 80% power to detect a clinically significant difference of 20% (40% in treatment vs. 20% in control arm) in the median percent change in NIHSS at 72 h, considering a standard deviation of 30%, at the two-sided statistical significance threshold of *p* = 0.05, when using a Wilcoxon-Mann-Whitney test. The primary null hypothesis is that there is no or negligible difference in clinical benefit between remote ischemic conditioning plus standard medical therapy and standard medical therapy alone.

### Data Monitoring Boards

An independent Data and Safety and Monitoring Board (DSMB) will be constituted by an experienced neurologist ([name]) of the Istituto di Ricerche Farmacologiche Mario Negri, a statistician ([name]) of the Istituto di Ricerche Farmacologiche Mario Negri and a lay member ([name]) of the Italian stroke patients' association A.L.I.C.E. Onlus (Associazione per la Lotta all'Ictus Cerebrale). The DSMB will provide expertise by periodical review and evaluation of the accumulated study data for participant safety, study conduct, and progress; it will monitor any serious adverse events, guarantee patient's dignity and fundamental rights with regard to treatments and care, and provide recommendations on continuation, modification, or termination of the trial.

### Data Analysis

The baseline patient characteristics of each treatment group will be described as means and standard deviations, medians, and quartiles, for numerical variables, and as frequencies and percentages per class for qualitative variables. Between-group unbalances among baseline characteristics will be considered for adjustment whenever deemed important for the outcome, in which case an adjusted secondary logistic analysis will be performed. The primary analysis of treatment effect on early neurological improvement will be performed using a Wilcoxon-Mann-Whitney test. Secondary analysis of the primary outcome will be performed using a mixed linear regression including treatment, centers, and any unbalanced baseline characteristics. Secondary outcomes will be analyzed using a Wilcoxon-Mann-Whitney test to evaluate treatment effect on early neurological improvement at 24 h or 48 h, and using a logistic mixed model to assess the effect of RIC on secondary variables (i.e., Wong-Baker face pain rating scale, modified Rankin scale, and occurrence of symptomatic intracerebral hemorrhage). The mRS scores will be dichotomized as a good functional outcome (mRS 0–2) and poor functional outcome (mRS 3–6). Wong-Baker Face Pain Rating Scale scores will be dichotomized around medians. Whole blood levels of HIF-1α mRNA and plasma levels of HSP27 in each arm will be represented by histograms. We expect no missing data for the primary outcome since patients will still be hospitalized. In case of missing results, a multiple imputation procedure will be used. Analyses will be conducted with an intention-to-treat approach (ITT). For the primary outcome, patients with neurological worsening will be given a percent change of 0; those deceased within 72 h will be given the last percent change available and a percent change of 0 will be assigned in case admission NIHSS is the only available data. A population of interest is composed of patients that completed the experimental intervention: a specific section will be devoted to this group, where main analyses will be repeated. The cut-off for statistical significance will be set at 0.05, two-tailed. Analyses will be carried out in blind using Stata/IC v. 15 or higher (Statacorp). A detailed Statistical Analysis Plan (SAP) will be written within 1 month after enrollment of the first patients.

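### The primary rank test uses neither site nor admission NIHSS, and the secondary model adds baseline covariates only when unbalanced: achievable efficiency is lost, but stated power and type I error hold

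*Protocol article*

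**What the plan says.** All places are in the protocol article.

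- **Randomization:** allocation is 1:1 by a "computer-generated block randomization schedule stratified by site". Selection/Treatment of Subjects names three hospitals.
- **Outcomes:** the primary outcome is the percent change in NIHSS from admission to 72 h, so admission NIHSS is its denominator.
- **Sample Size Estimates:** "An estimated total sample size of 80 patients (40 patients in each arm) should yield 80% power". The target is a "difference of 20% (40% in treatment vs. 20% in control arm) in the median percent change in NIHSS at 72 h". The assumed SD is 30 percentage points, and the calculation is for an unstratified, unadjusted Wilcoxon-Mann-Whitney test.
- **Data Analysis, primary:** "The primary analysis of treatment effect on early neurological improvement will be performed using a Wilcoxon-Mann-Whitney test". No stratum or covariate is mentioned. "The cut-off for statistical significance will be set at 0.05, two-tailed".
- **Data Analysis, secondary analysis of the primary outcome:** a "mixed linear regression including treatment, centers, and any unbalanced baseline characteristics".
- **Data Analysis, baseline imbalance:** imbalances are considered for adjustment if judged important for the outcome, "in which case an adjusted secondary logistic analysis will be performed". That sentence does not say which outcome it concerns.

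**The concern.** A factor used to stratify randomization is normally carried into the analysis, and a baseline measurement of the outcome scale, available for every patient, is the most obvious covariate. The primary test uses neither.

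Dividing by admission NIHSS removes its influence only if change is proportional to it. The protocol's own Discussion treats severity as prognostic, since it excludes scores below 5 because such strokes tend to recover spontaneously.

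The rule for the secondary model selects on the wrong property. A covariate earns its place by predicting the outcome, not by differing between arms. Under the stated rule a strong predictor that happens to be balanced stays out, and the adjusted model cannot be written down before the data are seen.

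At stake is precision in a trial of 80 patients whose Discussion concedes that the sample is small and that a neutral result would not exclude a milder effect.

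**Working it through.** **1. Reproduce the plan's figure.** Inputs from Sample Size Estimates: difference 20, SD 30, two-sided 0.05, power 80%, 1:1 allocation. Noether's formula:

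N = (1.960 + 0.842)² / [12 × 0.25 × (p − 0.5)²], with p = Φ(20 / (30√2)) = Φ(0.471) = 0.681.

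This gives N = 79.6, rounded to 80, with power 80.2% at 80. The stated figure holds for the stated test.

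**2. Assumptions for the comparison.** The documents give neither the share of variance due to site nor how well admission NIHSS predicts percent change. Both are varied: site 0 to 10%, baseline R² 0 to 0.3. Each setting had 4,000 simulated trials with 40 per arm, three sites, blocks of 4, difference 20 and SD 30. The Monte Carlo standard error near 82% is √(0.82 × 0.18 / 4000) = 0.6 points.

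**3. Site alone (baseline R² = 0).**

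| Site share of variance | Plain Wilcoxon power | Site-stratified (van Elteren) power | Difference |
|---|---|---|---|
| 0 | 82.5% | 81.2% | −1.3 |
| 5% | 82.0% | 82.3% | +0.3 |
| 10% | 83.3% | 84.8% | +1.5 |

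Type I error at 10% site variance is 0.038 for the plain test and 0.050 for the stratified one. Ignoring site makes the test slightly conservative.

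**4. Admission NIHSS (no site effect).** The trigger is modelled as adjusting only if the baseline imbalance has p < 0.05. That threshold is an assumption, because the article gives none. The last three columns are linear models that include site.

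| R² | Planned Wilcoxon | Site only | Site + admission NIHSS | NIHSS only if unbalanced |
|---|---|---|---|---|
| 0 | 82.5% | 84.6% | 84.4% | 84.4% |
| 0.1 | 81.9% | 83.8% | 87.4% | 84.1% |
| 0.2 | 81.6% | 83.8% | 90.7% | 84.3% |
| 0.3 | 82.0% | 83.4% | 93.8% | 84.8% |

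With outcomes floored at 0 (as Data Analysis prescribes for worsening) and capped at 100:

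| R² | Planned Wilcoxon | Site only | Site + admission NIHSS | NIHSS only if unbalanced |
|---|---|---|---|---|
| 0 | 82.2% | 82.5% | 82.0% | 82.4% |
| 0.1 | 81.6% | 81.8% | 85.6% | 82.0% |
| 0.2 | 80.9% | 81.0% | 88.0% | 81.8% |
| 0.3 | 79.7% | 80.0% | 91.6% | 81.3% |

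- Gain of prespecified adjustment over the planned test at R² = 0.1, 0.2, 0.3: 5.5, 9.1 and 11.8 points without the floor; 4.0, 7.1 and 11.9 with it. The floor reduces the gain at the two lower values.
- Part of the unfloored gain comes from using a linear model on normal data. Against the site-only linear model, the covariate itself adds 87.4 − 83.8 = 3.6, 90.7 − 83.8 = 6.9 and 93.8 − 83.4 = 10.4 points.
- At R² = 0 the covariate adds nothing (84.4 against 84.6; 82.0 against 82.5 with the floor).
- The imbalance trigger adds only 0.3, 0.5 and 1.4 points over the site-only model (unfloored), so nearly all of the gain is forgone. Its type I error was 0.043, 0.042 and 0.040: no inflation with one candidate covariate.

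**5. Rank version of the fix.** A separate simulation (4,000 trials per setting, site 5% of variance) gave the site-stratified rank ANCOVA 86%, 90% and 94% power at R² = 0.1, 0.2 and 0.3, against 82%, 83% and 83% for the plain Wilcoxon. The gains are 4, 7 and 11 points. Its type I error was 0.047 to 0.048.

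**The case against.** The strongest defence is that nothing in the primary analysis is wrong. It is one fixed test, the sample size was computed for that test, and the target is met. Site matters little. Admission NIHSS is already in the outcome, and the Discussion says percent change was chosen to account for the spread of admission scores. How much it still predicts is undocumented. One point being 20% at NIHSS 5 and about 4% at NIHSS 24 shows coarser steps for mild strokes, not that baseline predicts mean percent change. A covariate list belongs in the SAP, which the article promises.

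Most of this stands, and it rules out several stronger readings that a reader might infer:

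- **That the trial is underpowered or its type I error inflated.** Steps 1, 3 and 4 show neither.
- **That observed data choose the primary result.** They can shape only the secondary model. Imbalance must also be judged important for the outcome, and analysts are to be blinded.
- **That every covariate depends on imbalance.** Centers always enter the secondary model.
- **That the plan contradicts itself on logistic versus linear.** The logistic sentence names no outcome, and the same section uses logistic mixed models for secondary outcomes, with mRS and pain scores dichotomized. It is ambiguous, not contradictory.
- **That a mixed model with three centers fails.** The text does not say which terms are random, and this was not computed. It is a minor point.

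The SAP argument does not remove the concern. The article states the unadjusted test and the imbalance rule, so a later SAP would have to depart from them.

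**Conclusion.** The concern holds as a matter of efficiency and prespecification. The primary test leaves out the stratification factor and admission NIHSS, and the secondary model's imbalance rule omits prognostic covariates that happen to be balanced.

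The site part is worth about −1 to +2 points of power for 0 to 10% site variance. The admission NIHSS part runs from about nothing at R² = 0 to roughly 4 to 12 points at R² of 0.1 to 0.3. These sizes rest on assumed variance shares and on the protocol's own difference of 20 and SD of 30. The imbalance-rule result also rests on an assumed p < 0.05 trigger with a single covariate. The documents cannot say where in the range the trial lies.

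The change is worth making because it needs no new data and its worst case is small. It is not needed to rescue the stated power or error rate.

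**What to change.** 1. Make the primary analysis a site-stratified rank test adjusted for admission NIHSS, for example stratified rank ANCOVA. Keep the plain Wilcoxon-Mann-Whitney test as a sensitivity analysis. The 80 patients can stay.
2. In the secondary linear model, delete the imbalance trigger. Name in advance a covariate set that includes admission NIHSS, kept whatever the observed balance, and enter site as a fixed effect.
3. State that the adjusted logistic analysis applies only to the dichotomized secondary outcomes.
4. Record the change as a dated departure from the published plan, made before any unblinded look at outcomes.

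Cost: protocol or SAP wording, a slightly more complex primary test, and a possible loss of about 1 point of power if neither site nor admission NIHSS is prognostic (81.2% against 82.5% for the stratified test with no site effect).

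### The adjusted analysis of the primary outcome is a mixed model over three centers, so whether it adjusts for the randomization stratum depends on chance; fixed center terms would always do so

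*Protocol article*

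**What the plan says.** Under Selection/Treatment of Subjects, the protocol article limits recruitment to "three ISO-associated academic hospitals provided with Comprehensive Stroke Centers". Under Randomization, allocation is individual: "1:1 allocation as per computer-generated block randomization schedule stratified by site".

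Under Data Analysis, the primary test is named without any stratification: "The primary analysis of treatment effect on early neurological improvement will be performed using a Wilcoxon-Mann-Whitney test". The adjusted analysis follows: "Secondary analysis of the primary outcome will be performed using a mixed linear regression including treatment, centers, and any unbalanced baseline characteristics". The article names no other grouping factor for this model, and each patient contributes one value of the 72-hour outcome. It does not say outright that center is random, and it names no estimator and no small-sample correction. A logistic mixed model is planned for pain, modified Rankin scale and symptomatic hemorrhage. Further detail is deferred to a SAP that is not shown.

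**The concern.** With one outcome value per patient and no other cluster, center is the only natural random effect. A variance component over three units has 2 degrees of freedom. When its estimate falls on the boundary at zero, the fitted model contains no center term at all. The reader would then see a center-adjusted analysis that in fact adjusts for nothing at center level.

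The unstratified Wilcoxon-Mann-Whitney test does not use the strata, so this model is the only stated analysis of the primary outcome that does. At stake is whether that adjustment is carried out reliably and whether the adjusted interval for RIC has its nominal width.

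**Working it through.** **Inputs from the protocol article.** Three centers; 80 patients, 40 per arm; effect 20 points ("clinically significant difference of 20% (40% in treatment vs. 20% in control arm"); SD 30; two-sided 0.05; 1:1 blocks within site. **Assumed, because the article gives no figure:** center share of variance (ICC) 0 to 0.20, center sizes, normal outcome, number of added covariates *k*, and the estimator.

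**1. The plan's own figure.** Noether's formula for the Wilcoxon-Mann-Whitney test: P(X<Y) = Φ(20/(30√2)) = 0.681, so N = (1.960 + 0.842)² / (3 × 0.181²) = 79.6, that is 80. The stated sample size is reproduced, and center plays no part in it.

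**2. How often the center variance is estimated as zero.** Take equal centers of 80/3 patients and treatment balanced within center. Then F = MS(between)/MS(within) is distributed as λ·F(2, 76), with λ = 1 + (80/3)·ICC/(1 − ICC). REML gives zero when F ≤ 1. ML gives zero when F ≤ (3/2)(76/77) = 1.48. For 2 numerator degrees of freedom, P(F(2,76) ≤ x) = 1 − (1 + 2x/76)^(−38).

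At ICC 0.05, λ = 2.40. REML: x = 1/2.40 = 0.416, probability 34%. ML: x = 1.48/2.40 = 0.616, probability 46%.

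| ICC | ML, formula | ML, simulated | REML, formula | REML, simulated |
|---|---|---|---|---|
| 0.01 | 68% | 69-79% | 54% | 56-59% |
| 0.05 | 46% | 46-59% | 34% | 34-40% |
| 0.10 | 31% | 32-44% | 22% | 22-28% |
| 0.20 | 18% | 19-29% | 12% | 14-17% |

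The simulated ranges (3,000 trials per setting) cover center sizes 27/27/26 and 50/20/10; the higher ends come from the unequal pattern.

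**3. What a zero estimate does to the RIC interval.** RIC is compared within sites, so its standard error hardly depends on the center variance. In the same simulation:

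- Coverage of the 95% interval: ML with z 93.7-94.6%, REML with z 93.9-94.8%, fixed centers with t 94.4-95.4%.
- Leaving center out entirely: 94.9-96.4%, nominal to slightly conservative, because true center variation moves into the residual.
- In trials with a zero estimate at ICC 0.05 and equal centers: REML standard error 6.53 against 6.58 with fixed centers; ML 6.46 against 6.57. Over all settings, coverage within the zero-estimate trials was 93.1-95.4%.

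The small shortfall is also present at ICC 0, so lost center variance is not its cause.

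**4. Where the shortfall comes from.** With a zero center variance and *k* covariates, ML divides a residual sum of squares on 78 − *k* degrees of freedom by 80 and uses 1.960. Fixed centers use the unbiased variance and t on 76 − *k*. The expected half-width ratio is about √((78 − k)/80) × 1.960/t.

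- *k* = 0: 0.987 × 1.960/1.992 = 0.97
- *k* = 3: 0.968 × 1.960/1.993 = 0.95
- *k* = 6: 0.949 × 1.960/1.994 = 0.93
- REML with z keeps only the second factor: about 0.98.

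Simulation gave the same ratios. In absolute terms, the fixed-center half-width at SD 30 is about 1.992 × 30√(2/40) = 13.4 points, so 3% is about 0.4 points and 7% about 0.9 points.

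**5. Type I error with six covariates** (2,000 null trials per setting, Monte Carlo error about 0.5 points): ML with z 6.0-8.0%, REML with z 4.8-6.7%, fixed centers with t 4.0-5.7%.

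**The case against.** The strongest reply is that the article leaves the estimator, the degrees-of-freedom method and the coding of center to a SAP. On that view, ML with z is the reviewer's assumption and the rest is a modeling preference. This stands for the interval width: under REML with a small-sample correction, that part shrinks or disappears. It does not answer the main point. The article itself chooses a mixed model and fixes three centers, and REML still gives a zero estimate in about a third or more of trials at ICC 0.05.

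A second reply is that six covariates is an invented scenario. That is fair. The article gives no number and restricts adjustment to imbalances thought important for the outcome. With no covariates the ML shortfall is about 3%.

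A reader might also infer a causal chain: three centers, so the variance drops out, so the RIC interval is too narrow. The documents do not support this. Allocation is within site, and losing the center term if anything widens the interval. Intervals became clearly too short only when the RIC effect itself was made to vary by center (coverage 85.4% at a between-center SD of 10). The article describes no such term, and fixed center terms did no better there (86.1%).

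Finally, t inference is exact only under normal errors. The article sets worsening to a change of 0, which floors the outcome, and the simulations used an unfloored normal outcome. Either model is therefore approximate here.

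**Conclusion.** The point holds as a cheap improvement of low severity. If center is random, its variance is very poorly estimated on 2 degrees of freedom. Whether the stratum enters the fitted model is then close to a coin toss under ML at a 5% center share, and the term is lost in 35-40% of trials under REML. The share is assumed; the chance of losing the term falls as the share rises.

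To say that the variance cannot be estimated at all would go too far: it is nonzero in many trials, and a zero estimate is correct when centers do not differ. Nor is the RIC estimate biased. The interval shortfall is a separate matter of ML divisor and z reference: about 3% with no covariates, up to 7% with six, about 2% under REML with z. It depends on an estimator that the article does not name.

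The analysis concerned is secondary. The Wilcoxon-Mann-Whitney test and the sample size of 80 stand as they are.

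**What to change.** Replace the sentence in Data Analysis with: *The secondary analysis of the primary outcome will use linear regression with treatment, center as a fixed factor (two indicator terms) and the baseline covariates, with t-based confidence intervals.*

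This always adjusts for the randomization stratum, and in the six-covariate simulation it brings type I error from roughly 6-8% (ML with z) back to about 5%. It costs one sentence, 2 degrees of freedom (76 residual instead of 78 before covariates) and a slightly wider interval.

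If center is meant to be the random effect in the logistic mixed model as well, the same 2 degrees of freedom apply and the choice should be reconsidered there. That model was not simulated.
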